**Figure 1 F1:**
[figure not shown]
Flowchart of the IMPALA study.

### Ethical approval and informed consent

The Medical Ethical Committee of the University of Maastricht has granted ethical approval. The trial is registered as ISRCTN51556722 [43].

An information sheet will be given to all eligible patients. Patients will be informed on all aspects of the project by means of written information and personally at the inclusion. The privacy of the participating patients is protected, and all data will be coded and processed anonymously. It will be made clear in the informed consent form that each patient can terminate his or her participation the study at any moment. Patients will be asked to sign the informed consent form, and return this to Maastricht University to allow further contact regarding the research.

### General practices

Inclusion criteria for the general practices are that they have to employ a practice nurse and work with electronic patient records. Practices will be invited by letter to participate in the trial. Addresses will be obtained from the NIVEL (Netherlands Institute for Health Services Research) database. If a practice expresses interest, it will be visited by members of the project team for further information and explanation about the study. Non-responding GPs will be reminded after 1 month, by renewed postal invitation. The general practices will be located in the central and southern parts of the Netherlands. In the Netherlands, all patients are obliged to be registered with a general practice.

### Participants

The inclusion criteria for participants are based on the Dutch guideline for CVRM. According to the guideline, the following patients are eligible for a cardiovascular risk assessment:

Especially patients

• who have high blood pressure (≥ 140 mmHg) or are already being treated for it; and/or

• who have high total cholesterol (≥ 6.5 mmol/l) or already being treated for it; and/or

• who are smokers (men ≥ 50 years, women ≥ 55 years); and/or

• who have diabetes.

In addition, patients:

• who have positive family history of CVD; and/or

• who have visible obesity.

Patients with existing cardiovascular diseases, patients at high risk based on familial hypercholesterolaemia only and patients who are primarily managed in secondary care (e.g. by cardiologists or internists or in rehabilitation programmes) will be excluded from the study. This is a clinical approach to primary prevention. We will not manipulate the process of identifying potential high-risk patients other than by informing the GPs about the inclusion criteria, to stimulate usual strategies for case finding, either by the GPs during consultation hours or by the nurses inviting high-risk patients from available patient records. To facilitate the inclusion process, the GPs and practice nurses will receive a chart stand, with the inclusion criteria which they can place on their desk.

### Sample size calculation and feasibility of recruitment

The study will be powered on outcomes on patient behaviour to detect an absolute 52-week, post-intervention, between-group difference of 15% (50 – 65%) in patients' self reported adherence to life-style advice on smoking, diet, alcohol and physical exercise (alpha = 0.05, power = 0.80). The figure of 50% represents the average adherence by patients with chronic diseases [13]. The power calculation for clustered data analysis assumes an intra-class correlation coefficient (ICC) of 0.04. ICC values in earlier trials among general practitioners were 0.06 [44] and 0.03 [45]. Since we expect that the nurses will perform well in terms of adhering to the working protocol, we expect a lower ICC, with a maximum of 0.04. Thus, the within-cluster variance will be almost equal to the between-cluster variance. This implies that 600 patients are needed (300 per group) at 52 weeks. It is our intention that a total of 720 patients will be recruited by the GPs or practice nurses, to compensate for an expected 15% loss to follow-up (in an earlier trial by [name], 87% of the included patients responded at the 6-month follow-up [45]). It should be possible to prospectively recruit 720 patients (36 per practice) in 6 months, as Dutch general practices each have 100–150 of these patients, who visit the practice at least once a year for regular monitoring.

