## Methods

### Design

The IMPALA study is a cluster-randomised controlled trial involving 20 general practices and 720 patients in the Netherlands. An independent statistician will perform a central block randomisation. Practices will be randomly allocated, 10 practices to the intervention group and 10 practices to the control group, after stratification into 4 geographical regions. Assessments will be made at the inclusion of the patients in the study, at 12 weeks and at 52 weeks. A flowchart of the study is shown in Figure 1.

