### Data analysis

Since it is not possible to restrict our study to one primary outcome for all patients beforehand, the study will examine 6 different lifestyle changes: smoking, physical exercise, fat intake, fruit, vegetables and alcohol.

To assess the difference in primary outcomes between the arms, the arms will first be compared in terms of changes in the specific lifestyle issues, independent of the targets chosen by the intervention patients. We will use a T test for continuing variables and a χ^2 ^test for dichotomous variables.

A second analysis of primary outcomes is a multilevel regression analysis (using SPSS and MLwin), which uses adherence to the primary outcomes of lifestyle change as the dependent variables and group allocation and pre-intervention scores as independent variables. Additional independent variables will be included in the model, such as patient characteristics (age, sex, anxiety and risk of CVD). Additional regression analyses will focus on the effect at T2.

The third analysis involves constructing a simple standardised overall adherence score for the six lifestyle items, which expresses to what extent, on average, patients achieved the behaviour change goals of the national recommendations for a healthy lifestyle. The score of the intervention group will be compared with that of the control group.

Finally, the reduction in the 10-year risk of CVD will be analysed for differences between the two arms. The risk of CVD will be analysed with a multilevel regression analysis, which uses the risk at 52 weeks as the dependent variable and group allocation and pre-intervention risk as independent variables.

The secondary outcomes will also be analysed for the differences between the arms, using a T test for continuing variables and a χ^2 ^test for dichotomous variables. We also intend to use a multilevel regression analysis (using MLwin) which uses e.g. self-efficacy and attitudes at T1 as the dependent variables and group allocation and pre-intervention scores as independent variables. Additional independent variables, such as patient characteristics (age, gender, risk of CVD and socio-economic status), will also be included in the model. Additional regression analyses will focus on the effect at T2. Further analyses for subgroups of patients are also possible.

In addition, we will describe the personal targets of the patients in the intervention arm, which will be recorded by the nurses.

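### The trial is powered on 52-week adherence, but the first-listed primary analysis compares unadjusted changes; the more precise baseline-adjusted 52-week model should be named as the main analysis

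*Protocol article*

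**What the plan says.** The section on sample size and recruitment sets the target "to detect an absolute 52-week, post-intervention, between-group difference of 15" percentage points, from 50% to 65% adherent ("alpha = 0.05, power = 0.80"). It "assumes an intra-class correlation coefficient (ICC) of 0.04" and concludes: "This implies that 600 patients are needed (300 per group) at 52 weeks". The target is therefore a difference in level at one named time.

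The Data analysis section of the effect evaluation lists several comparisons of the primary outcomes:

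- First, "the arms will first be compared in terms of changes in the specific lifestyle issues", by t test or chi-square test. No time point and no baseline covariate are given.
- Second, a multilevel regression that "uses adherence to the primary outcomes of lifestyle change as the dependent variables and group allocation and pre-intervention scores as independent variables". No time point is named for it either. The effect at T2 (52 weeks) follows as the subject of additional regressions.
- Third, a between-arm comparison of an overall adherence score across the six lifestyle items.

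For 10-year cardiovascular risk, the same section goes straight to a multilevel regression of the 52-week value with baseline risk as covariate. Table 1 lists the dichotomous behaviours as proportions (smoking, or meeting a recommendation), not as categories of change.

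**The concern.** The analysis closest to the sample size target is adherence at 52 weeks, adjusted for its baseline value and for practice. In the article it is neither first nor marked as the main one. The comparison placed first ignores the baseline value as a covariate and names no time. A reader cannot tell which result answers the question the trial was sized for. If the first-listed one is taken as the answer, precision that the trial already has the data to gain is given up.

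A smaller point concerns the chi-square test. The text speaks of changes, but change in a yes/no behaviour has three values: improved, unchanged or worse. The article does not say whether the test is applied to such categories, to a recoded version of them, or to the follow-up proportions that Table 1 suggests.

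**Working it through.** **Inputs from the article.** 50% against 65% at 52 weeks; two-sided alpha 0.05 (sidedness is not stated, two-sided is assumed); ICC 0.04; "10 practices to the intervention group and 10 practices to the control group"; 300 per arm at 52 weeks, so 30 per practice.

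**Assumptions not in the article.** The correlation r between the T0 and 52-week values, taken from 0.3 to 0.7. Adherence of 50% at T0 in both arms. The same design effect for all three comparisons.

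**The plan's own figure.** Two-sided, pooled variance, 80% power: 170 per arm before clustering. Design effect 1 + (30 − 1) × 0.04 = 2.16. 170 × 2.16 = 367.2, so 368 per arm or 736 in total. The stated 600 is not reproduced from the stated inputs. That is a separate matter; 300 per arm is used here as given, and the effective size is 300/2.16 = 138.9 per arm.

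**Target effect.** Expected difference in mean change = (65 − 50) − (50 − 50) = 15 points, the same as the difference in level.

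**Variances, summed over the two arms.**

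- Level at 52 weeks: 0.50 × 0.50 + 0.65 × 0.35 = 0.4775.
- Change: in each arm p0(1 − p0) + p2(1 − p2) − 2r√[p0(1 − p0)p2(1 − p2)]. Summed: 0.9775 − 0.977r.
- 52-week level adjusted for T0: approximately (1 − r²) × 0.4775.

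With equal variances at both times these are in the ratio 1 : 2(1 − r) : (1 − r²). Change against adjusted level is then 2(1 − r)/[(1 − r)(1 + r)] = 2/(1 + r), which exceeds 1 for every r below 1. Change equals the raw level where 0.9775 − 0.977r = 0.4775, at r = 0.51.

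**Power** = Φ(0.15/√(variance/138.9) − 1.96):

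| r | Level only | Change | T0-adjusted level | Variance, change ÷ adjusted |
|---|---|---|---|---|
| 0.3 | 0.73 | 0.57 | 0.77 | 0.684/0.435 = 1.58 |
| 0.5 | 0.73 | 0.72 | 0.84 | 0.489/0.358 = 1.37 |
| 0.7 | 0.73 | 0.90 | 0.95 | 0.294/0.244 = 1.21 |

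With a pooled variance the level-only power is 0.72.

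**If, and only if, the chi-square test is run on three categories of change.** Its power with 2 degrees of freedom at the same effective size is 0.47, 0.62 and 0.87 at r = 0.3, 0.5 and 0.7. That is below the comparison of mean change at each r.

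All these powers allow for clustering through the design effect. They compare the three outcome definitions on an equal footing. They are not the powers of the t and chi-square tests as listed, which are stated without any allowance for clustering.

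**The case against.** The strongest reply is that the remedy is already planned. The second analysis adjusts for baseline and for practice, and it is extended to 52 weeks. The article nowhere says that the first-listed comparison is decisive; first, second and third may be no more than an order of presentation. This stands in large part and limits the harm. It does not settle which analysis answers the sample size question, and the 52-week version is still described as additional.

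A reader might go further in four ways that the article does not support:

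- **That the powered contrast is not tested at all.** Mean change to 52 weeks has the same expected between-arm difference as the 52-week level, and the second and third analyses also concern the primary outcomes.
- **That precision is always lost against the powered contrast.** This depends on r. Change is worse than the raw level below about 0.5 and better above it (0.90 against 0.73 at r = 0.7). Only the loss against the baseline-adjusted value is unconditional.
- **That the chi-square test is three-valued and would miss an effect on relapse.** The article applies it to dichotomous variables, Table 1 lists proportions, and the section uses the word change loosely for the behaviours themselves. The coding is ambiguous, not known to be wrong.
- **That chance baseline imbalance is a further, separate harm.** It is already part of the change-score variance. With 360 per arm at T0 and design effect 1 + 35 × 0.04 = 2.40, the standard error of a T0 difference is √(0.5 × 2.40/360) = 5.8 points. At r = 0.5 such an imbalance moves change by (1 − 0.5) × 5.8 = 2.9 points and the unadjusted level by 0.5 × 5.8 = 2.9 points, the same size.

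**Conclusion.** The point holds as an improvement available at almost no cost, not as an invalid analysis. The sample size concerns adherence at 52 weeks; the comparison listed first concerns unadjusted change at an unstated time. The effect aimed at is the same, but unadjusted change has about 1.2 to 1.6 times the variance of the baseline-adjusted 52-week value for r between 0.7 and 0.3. In power this is 5 points at r = 0.7, 12 to 13 points at r = 0.5 and about 20 points at r = 0.3.

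These sizes rest on an assumed r, on 50% adherence at T0 in both arms, on one common design effect and on a normal approximation. The direction against the adjusted analysis does not depend on the value of r. The shortfall of the raw level comparison from 80% to about 73% comes from the sample size arithmetic, not from the use of change. The wording on the chi-square test needs clarifying on either reading.

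**What to change.** In the Data analysis section of the effect evaluation:

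- Name one main analysis for each lifestyle outcome: the multilevel regression of the 52-week value on group, with the T0 value as covariate. Use a linear model for scores and a logistic model for dichotomous behaviours. The section already does this for 10-year cardiovascular risk.
- For dichotomous behaviours, report a standardised 52-week difference in proportions, so that the result is on the scale of 50% against 65%. A logistic model does not give this directly. It needs one further step: average the predicted probabilities over all patients under each allocation and take the difference.
- State that dichotomous behaviours are compared as 52-week proportions.
- Present changes from baseline as description only.

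The cost is a few sentences. The T0 and 52-week questionnaires and the multilevel model are already planned, so no patients, visits or data are added.

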The patients in the intervention arm will probably notice the attempts to promote patient involvement and the changes in the relationship between health professional and patient and in the communication during the consultations. In an earlier community-oriented and individual-oriented prevention project for cardiovascular diseases in the Dutch province of Limburg, frictions and irritations were found among both health advisors and patients in the consultations [40]. In this project, the research agenda had determined a large part of the agenda setting of the prevention activities, and the options for risk reduction were limited to certain themes. In the context of CVD prevention, a deliberative model of the relationship between physician or practice nurse and patient is preferable to other models of the physician-patient relationship [41]. In this model, the aim of physician-patient interaction is to help the patient determine and choose the best health-related values that can be achieved in the clinical situation. The role of the physician is that of a teacher or a friend, engaging the patient in a dialogue on the best course of action. The IMPALA project will involve interviews in which patients will be asked about their experiences with and opinions about the IMPALA intervention, so that this can be evaluated from an ethical perspective.

We hypothesise that the intervention will modify patients' adherence to lifestyle advice, but the intervention may also improve the healthcare process implemented by GPs and practice nurses and hence the amount of time and effort required from the professionals [42]. Since this study will determine both the effects and the costs of the implementation of the nurse-led intervention an economic evaluation of the intervention is planned to compare the cost-effectiveness ratio in the intervention group with that in the control group.

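### With the plan's own inputs (50% vs 65%, ICC 0.04, 20 practices), 600 analysed patients give about 72% two-sided power, not 80%, and the supporting variance statement is wrong

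*Protocol article*

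**What the plan says.** The section on sample size and feasibility of recruitment powers the trial on self-reported adherence to lifestyle advice at 52 weeks. It targets a rise from 50% to 65% with "alpha = 0.05, power = 0.80". It does not say whether alpha is one- or two-sided. It assumes an ICC of 0.04, described as the expected maximum, and cites 0.06 and 0.03 from two earlier trials.

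From the ICC it draws this inference: "Thus, the within-cluster variance will be almost equal to the between-cluster variance". The next sentence gives the result: "This implies that 600 patients are needed (300 per group) at 52 weeks". Recruitment is set at 720 (36 per practice) to allow for 15% loss. The support for that loss figure is an earlier trial in which "87% of the included patients responded at the 6-month follow-up".

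The Design section fixes 20 practices, 10 per arm.

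**The concern.** The paragraph gives both its inputs and its result, so the result can be checked, and the two do not agree. A 15-point difference around 50% to 65% needs roughly 170 patients per arm without clustering. An ICC of 0.04 with 30 patients per practice more than doubles that, to well above 300.

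The variance sentence is a separate error. An ICC of 0.04 means that very little of the variance lies between practices. Near-equal components would mean an ICC of about 0.5. The sentence stands directly before the sample size as part of its derivation, which casts doubt on how clustering was handled.

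If the true power is lower than stated, the chance of missing a real 15-point effect is about 28% to 32% rather than 20%. Readers would then give a null result more weight as evidence of no effect than the design supports.

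**Working it through.** **Inputs**

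- From the sample size section: p1 = 0.50, p2 = 0.65, alpha 0.05, power 0.80, ICC 0.04, 300 analysed per arm, 720 recruited, 15% loss.
- From the Design section: 10 practices per arm, hence m = 600/20 = 30 analysed per practice.
- Assumed: a two-sided test, equal cluster sizes, no covariate adjustment.

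**Step 1. Unclustered sample size.** With mean proportion 0.575,

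n = [1.96·√(2 × 0.575 × 0.425) + 0.8416·√(0.25 + 0.2275)]² / 0.15² = 169.3 per arm (170 rounded up; 166.6 with unpooled variance).

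**Step 2. Design effect.** 1 + (30 − 1) × 0.04 = 2.16.

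**Step 3. Required number.** 169.3 × 2.16 = 365.7, so 366 per arm and 732 in total. Other variance choices give:

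| Method | Per arm |
|---|---|
| Unpooled variance | about 360 |
| Arcsine | 365 |
| Continuity correction | 395 |

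None gives 300. Step 3 holds 30 patients per practice, so it implies 170 × 2.16 / 30 = 12.24, that is 13 practices per arm. With 10 practices per arm fixed, m must satisfy 10m = 170 × [1 + (m − 1) × 0.04]. That gives m = 51, or 1,020 analysed patients.

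**Step 4. Attempts to reproduce 300 per arm**

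- Solving for the ICC: (300/169.3 − 1)/29 = 0.027, below both cited values.
- One-sided alpha 0.05: 133.2 × 2.16 = 287.8 per arm, 576 in total. This is near 600 but not equal to it.
- Cluster size 20: 170 × (1 + 19 × 0.04) = 170 × 1.76 = 299.2. This matches, but it would describe 30 practices of 20, or the number of practices used as the cluster size. It contradicts 20 practices of 30, and that this is how 600 arose is only conjecture.

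**Step 5. Power of 300 per arm.** Effective n = 300/2.16 = 138.9 per arm.

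- Normal approximation: z = [0.15·√138.9 − 1.96·√(2 × 0.575 × 0.425)] / √0.4775 = (1.768 − 1.370)/0.691 = 0.575, so power is 71.7%.
- Non-central t with 20 − 2 = 18 degrees of freedom: noncentrality 0.15/√(0.4775/138.9) = 2.558, so power is 67.7%.
- Difference detectable from 50% at 80% power: 16.5 points (normal) or 17.2 points (18 df).

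**Step 6. Sensitivity.** Two-sided power, normal approximation / t with 18 df:

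| Analysed (per practice) | ICC 0.03 | ICC 0.04 | ICC 0.06 |
|---|---|---|---|
| 600 (30) | 78% / 74% | 72% / 68% | 61% / 58% |
| 612 (30.6), 15% loss from 720 | 78% / 74% | 72% / 68% | 62% / 58% |
| 720 (36), no loss | 81% / 78% | 75% / 71% | 64% / 60% |
| 545 (27.25), 24% loss from 720 | 76% / 72% | 70% / 66% | 60% / 56% |

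The last row assumes that the cited 13% loss over six months recurs in the next six: 0.87² = 0.757, and 720 × 0.757 = 545. The documents neither state nor exclude that rate.

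**Step 7. Recruitment allowance.** 600/0.85 = 706, which is below 720. The inflation for 15% loss is adequate.

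**Step 8. Variance components.** ICC = between/(between + within) = 0.04 gives between/within = 0.04/0.96 = 1/24. Equal components give ICC = 0.5.

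**The case against.** The strongest reply is that sidedness is not stated. With a one-sided 5% test, 600 patients give 81.4% power (79.3% with 18 df), close to the claim. But no one-sided test is mentioned anywhere. The Data analysis section plans t and chi-square tests ("We will use a T test for continuing variables"), and the Background words the hypothesis without direction: "We hypothesise that the intervention will modify patients' adherence to lifestyle advice". Two-sided is the fair reading, though it remains an assumption.

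The multilevel model also adjusts for pre-intervention scores, which can recover power. If adjustment multiplies the variance by 1 − r², a baseline correlation of about 0.42 would restore 80% (about 0.50 with 18 df). This stands as a limit on the finding: the planned adjusted analysis may do better than 72%. It does not rescue the calculation, because the sample size section neither invokes adjustment nor gives a correlation.

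Three smaller points also have merit:

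- The 18-df figure is a small-sample refinement that the protocol does not adopt. The finding rests on 72% alone.
- An ICC of 0.04 lies between the two cited values and comes with a reason. It is optimistic as a maximum when 0.06 has been observed, but it is not an arithmetic error.
- The 15% loss allowance exceeds the cited 13%, and the 24% scenario is an assumption that moves power by only about two points.

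None of these replies touches the variance sentence, which is wrong whatever the sidedness.

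**Conclusion.** The concern holds. Under a two-sided 5% test, ICC 0.04 and 20 practices of 30 analysed patients, 600 patients give 71.7% power for 50% vs 65% (67.7% with 18 df), and 80% power only for a difference of about 16.5 to 17 points. With 600 analysed, power falls short of 80% at every ICC the protocol names. At the planning ICC it stays short even if all 720 patients are retained.

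The statement that the two variance components are nearly equal contradicts the ICC beside it by a factor of 24. What is shown is that the stated inputs do not yield the stated number and power. The conclusion assumes a two-sided test, equal practice sizes and no gain from baseline adjustment. The ICC and attrition remarks are secondary, and the conclusion does not depend on them. Because a headline design property is contradicted by its own inputs, the paragraph must be corrected.

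**What to change.** Rewrite the sample size paragraph as follows.

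1. State that alpha is two-sided.
2. State that 600 analysed patients in 20 practices, at ICC 0.04, give about 70% power for 50% vs 65% (72% by normal approximation, 68% with 18 df), or 80% power for a difference of about 16.5 to 17 points. Give the cluster size of 30 and the design effect of 2.16.
3. Show the range for ICC 0.03 to 0.06 and for 15% to 24% loss. From 720 recruited, the normal approximation runs from 78% (ICC 0.03, 15% loss) to 60% (ICC 0.06, 24% loss). Label the 24% figure as an assumption.
4. Replace the variance sentence with a statement that between-practice variance is about 1/24 of within-practice variance.
5. If baseline adjustment is to be credited with restoring power, state the assumed correlation and its source.

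The cost is wording only. No extra patients or practices are needed and the analysis does not change, but the stated power becomes less favourable.
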